#### Processing

Data processing is the act of preparing the data from its raw format into a usable format by the machine learning models. Indications for data processing will include (1) making the data easier to use; new indicators will need to be created to facilitate their use as predictors, (2) reducing computational cost of many algorithms by decreasing the number of variables, especially correlated and collinear variables, (3) removing noise due to outliers, and (4) making the results easier to understand.

### Algorithms

The most common methods by which algorithms learn about data to make predictions are supervised, unsupervised, and semisupervised learning [1]. Supervised learning trains algorithms using example input and output data, previously labeled by humans. Data may be labeled—a term used to denote that the outcome (or class) is known (eg, ASHA has completed the training module or not completed the training module)—or unlabeled. In contrast, unsupervised learning is concerned with uncovering structure and patterns within complex datasets based on information that is neither classified nor labeled. In unsupervised machine learning, the algorithms learn to infer structure based on unlabeled input data using clustering techniques. Semisupervised learning is a hybrid analytic technique, applied in contexts where the majority of data points are missing outcome information and yet prediction remains the goal [1].

In this program context, supervised machine learning algorithms are expected to be the primary analytic method employed because analyses are focused on classification using predictors and available data are expected to be labeled. The transformation of variables may be achieved by a variety of techniques including the creation of composite indicators and box-cox transformations. Unsupervised machine learning techniques, including dimensionality reduction techniques such as principal components analysis or K-means clustering, will be carried out as appropriate. Principal component analysis uses an orthogonal transformation to convert a set of observations of possibly correlated variables into a set of values of linearly uncorrelated variables called principal components. The first principal component has the largest possible variance and accounts for the highest proportion of the variance in the data, with each succeeding component accounting for the highest variance possible after accounting for the previous components. K-means clustering is a way to use data to uncover natural groupings within a heterogeneous population (Table 1). To uncover patterns, the algorithm starts by first assigning data points into random groups. The group centers are then calculated, and the group memberships are re-assigned based on the distances between each data point and the group centers. This process is repeated until there are no changes in the group memberships from the previous iteration [16]. In its application to Mobile Academy, K-means clustering will be used to detect patterns in ASHA engagement with training content, including training initiation and completion. Among Kilkari users, K-means clustering will be used to assess patterns in exposure to content by user characteristics based on data elements available in the RCH, including parity, age, and geographic area.

**Table 1 table1:** Sample of data elements by source for Kilkari & Mobile Academy.

Database	Description	Sample of data elements anticipated for use in analyses	Variables	Boxes with reference to Figure 1
MCTS and RCH databases	National databases on reproductive, maternal newborn and child health care seeking among mothers and children <5 years of age Physically located in the NIC data center in Delhi	District, Mother & child unique IDs Pregnancy IDs ASHA IDs Last menstrual period Date of birth of child	Geographic identifiers Unique episode / beneficiary identifier	DB2, DB3
MOTECH database	Program database containing data on women and children as well as registered ASHAs Database works in conjunction with two algorithms, Kilkari and Mobile Academy, which function as “engines” for running the program Physically located in Railtel data center, Gurugram, Haryana	Kilkari: Activation date Deactivation date Calls answered Duration of content heard per message Mobile Academy: Course start date Course completion date Chapter wise scores Notification retry count Course passing date	Kilkari: Duration of enrollment in the program Status of enrollee Mobile Academy: Time taken to finish course Performance score of ASHA Number of tries by ASHA to complete modules	DB4
IVR database	Records when calls are triggered, what happens after the call is triggered (ie, does it get answered or does it fail, and if it fails why has it failed, eg, network errors, device errors) and whether the call needs to be retried; if yes, how many times. Records similar data for incoming calls. Physically located in Railtel data center, Gurugram, Haryana	Kilkari: Content file name Message duration Mobile Academy: Content identifier Duration of listening	Kilkari: Message identifier Duration of listening to message Mobile Academy: Content identifier Duration of listening	DB6
Call records database	Operator database on call handling Physically located in the Reliance data center, New Delhi	Call status Call failure reasons Call start time Call stop time Additional elements	Duration of listening to content	DB7

### Training of Algorithms

Once data have been processed, testing of algorithms will be carried out. Table 2 summarizes the algorithms proposed for training along with their intended applications to Mobile Academy and Kilkari. To determine the model with the best fit, we will explore several machine learning approaches in turn. Models will be fit on the training set, and the fitted model used to predict the responses for the observations in the validation set. The preferred analytic approaches will be selected based on their ability to minimize the total error of the classification, where the latter is defined as the probability that a solution will classify an object under the wrong category. We describe each approach considered below in lay terminology, along with indications for use, and its proposed application in the evaluations of Mobile Academy and Kilkari.

**Table 2 table2:** Summary of algorithms proposed for testing and their intended application to Mobile Academy and Kilkari.

Algorithm		Description	Intended evaluation application	
			Mobile Academy	Kilkari

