#### Splitting Into Training and Testing

To avoid overfitting models that work well for the data in hand but fail to predict well with other datasets, the data will be split into three components. This is possible due to the large size of the dataset. The training set will comprise 60%, the test dataset 20%, and the validation dataset 20% of the data. The test set will be used to test and fine-tune the accuracy of predictive models, and the final selected model will be applied to the validation dataset. We anticipate having data from 2017, 2018, and 2019 and will ensure equal representation by random sampling. To ensure that the data are controlled for time as a confounder, subsets will be equally represented across different time periods.

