### Testing and Validation

To facilitate decision making on the optimal analytic approach, three steps will be undertaken: (1) develop the correct model for each algorithm using the training dataset, (2) apply the final model for each algorithm on the test dataset, and (3) apply the best performing algorithm on the validation dataset.

In Step 1, algorithms will be run using the training dataset comprising 60% of the total sample from across all states for which data are available. For each algorithm, iterative testing will be run to select the best model that fits the data. The emerging results will then be assessed for model fit and accuracy. Table 4 summarizes the four proposed metrics for assessing the performance of each model.

**Table 3 table3:** Performance comparisons of learning algorithms modified from Kotisiantis et al [17,18] (++++ represents the best and + the worst performance).

Model attributes	Decision trees	NNs	Naïve Bayes	SVM	Linear discriminant analysis	Logistic regression
Accuracy in general	++	+++	+	++++	+++	++
Speed of learning with respect to number of attributes and number of instances	+++	+	+++	+		
Speed of classification	++++	++++	++++	++++	++++	++
Tolerance to missing values	+++	+	++++	++	+++	+
Tolerance to irrelevant attribute	+++	+	++	++++	+++	+
Tolerance to redundant attributes	++	++	+	+++	++	+
Tolerance to highly interdependent attributes	++	+++	+	+++	++	+
Dealing with discrete/ binary/ continuous attributes	++++	+++ (not discrete)	+++ (not continuous)	+++ (not discrete)	++++	+++
Tolerance to noise	++	++	+++	++	+++	++
Dealing with danger of overfitting	++	+	+++	++	++	+
Attempts for incremental learning	++	+++	++++	++		
Explanation ability/ transparency of knowledge/ classification	++++	+	++++	+	+	+
Model parameter handing	+++	+	++++	+	++	+

**Table 4 table4:** Metrics for assessing the performance of each model.

Model metrics	Formula^a^	Description
Accuracy	(TP+TN)/(TP+TN+FN)	Proportion of cases correctly classified
Precision or positive predictive value	TP/(TP+FP)	Fraction of relevant instances among the retrieved instances
Sensitivity or recall	TP/(TP+FN)	Fraction of relevant instances retrieved over total amount of relevant instances

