Area under receiver operating characteristic curve (AUROC)	Area covered by the function of true positive rate/ false positive rate	The curve is plotted and area between the curve and the 45° line is multiplied by 2 to give the AUROC. A value of 1 represents perfect accuracy while 0.5 means the prediction is worthless.

^a^TP: true positive, TN: true negative, FP: false positive, FN: false negative

To illustrate the definition of performance metrics for Mobile Academy, we define true positives (TP) as the number of correctly classified ASHAs who have completed the training, and true negatives (TN) as the number of correctly classified ASHAs who have not completed the training. False positives (FP) are defined as the number of ASHAs incorrectly classified as having completed the training, while false negatives (FN) are the number of ASHAs incorrectly classified as not having completed the training.

Results from the performance metrics will help define the final model for each algorithm. In Step 2, these final models for each algorithm will be applied to the test dataset, which comprises approximately 20% of the total data. Using the same performance metrics, the models with the best fit and accuracy will be applied to the validation dataset as part of Step 3. Ultimately, predictions for Mobile Academy will aim to determine the probability of the ASHA finishing the course in a predetermined time frame and the possible score/performance of the individual ASHAs. For Kilkari, we will determine predictors for exposure to Kilkari content based on user characteristics, as well as explore the effect of early listening patterns on postpartum engagement and overall exposure.

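### The validation set is assigned both to selecting algorithms and to the final check after selection, and two sections disagree on where tuning takes place

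*Protocol article*

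**What the plan says.** Three sections of the protocol article describe how the data subsets are used.

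- **Splitting Into Training and Testing** defines the sets: "The training set will comprise 60%, the test dataset 20%, and the validation dataset 20% of the data". It gives the middle set the development role, "The test set will be used to test and fine-tune the accuracy of predictive models", and keeps the last set for afterwards: "the final selected model will be applied to the validation dataset".
- **Training of Algorithms** says that models are fitted on the training set, with "the fitted model used to predict the responses for the observations in the validation set". The next sentence gives the selection rule: "The preferred analytic approaches will be selected based on their ability to minimize the total error of the classification". The test set is not mentioned in that account.
- **Testing and Validation** sets out three numbered steps. In Step 1, "algorithms will be run using the training dataset comprising 60% of the total sample", and "For each algorithm, iterative testing will be run to select the best model that fits the data". The Table 4 metrics then help to settle one version of each algorithm. Step 2 applies those versions to the test set. In Step 3, "the models with the best fit and accuracy will be applied to the validation dataset".

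**The concern.** A held-out set gives an honest estimate of performance only if it played no part in choosing what is being evaluated. The article names three sets and gives their sizes before it uses the terms, so the validation set in Training of Algorithms cannot easily be read as a loose word for any held-out data. An analyst who follows that section chooses the winner on the 20% that the other two sections keep for the final check, and no data are then left for an independent estimate.

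The second conflict concerns tuning within an algorithm. One section tunes on the test set. Another settles each algorithm's version in Step 1, on the training set, before the test set is used. If the Step 1 metrics are computed on the rows used for fitting, they reward flexibility for its own sake, which is the overfitting that the split is meant to prevent. The classifiers are a main product of the work, and the article presents itself as a reference for practitioners, so readers may copy the sequence as printed.

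**Working it through.** The article gives no number of records, error rate or target performance for these models, so there is no figure of its own to reproduce. The split adds up: 60% + 20% + 20% = 100%.

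**1. The sections side by side**

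| Section | Tuning within an algorithm | Choice between algorithms | Validation set used for |
|---|---|---|---|
| Splitting Into Training and Testing | test set | before the validation set is used | the model already selected |
| Training of Algorithms | not stated | lowest error, after prediction in the validation set | selection |
| Testing and Validation | Step 1, training set | Step 2, test set | Step 3, after selection |

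The first and third rows agree on the validation set, and the second does not. The first and third rows disagree on where tuning happens.

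**2. Optimism if selection and reporting share the validation set**

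Inputs: six supervised algorithms (Table 2). Assumed: all six have the same true accuracy of 70%, and their errors are independent. For n validation records, SE = √(0.7 × 0.3 / n). The expected maximum of six independent standard normals is 1.267, so the expected optimism is 1.267 × SE.

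| n in validation set (assumed) | SE | Optimism in accuracy |
|---|---|---|
| 200 | 0.0324 | 4.1 points |
| 1,000 | 0.0145 | 1.8 points |
| 100,000 | 0.0014 | 0.2 points |

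A binomial simulation, with true error assumed at 0.20 and at 0.40, agrees:

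| Total records | Validation records (20%) | Optimism, true error 0.20 to 0.40 |
|---|---|---|
| 1,000 | 200 | 3.5 to 4.4 points |
| 10,000 | 2,000 | 1.1 to 1.4 points |
| 100,000 | 20,000 | 0.36 to 0.44 points |
| 1,000,000 | 200,000 | 0.11 to 0.14 points |

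Six algorithms scored on the same records will have correlated errors, which makes these figures smaller.

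**3. Cost of in-sample scoring in Step 1, if that is what is meant**

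A simulation used a 60/20/20 split, four normal predictors of which two affect a binary outcome, and a k-nearest-neighbour classifier with k chosen from 1, 5, 15, 51 and 101. This classifier is not on the article's list and serves only as an illustration. There were 20 replicates at 1,000 records and 5 at 10,000.

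| Total records | Validation error, k chosen on training rows | Validation error, k chosen on test set | Difference |
|---|---|---|---|
| 1,000 | 0.394 | 0.326 | 6.8 points |
| 10,000 | 0.401 | 0.318 | 8.3 points |

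Scoring on the fitted rows always chose k = 1, with training error 0.00. Unlike the selection optimism in part 2, the penalty did not shrink at the larger size.

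An extreme case for a listed method: a fully grown tree on distinct continuous predictors reaches 100% training accuracy on pure noise. At an assumed 60/40 prevalence, its true accuracy is 0.6² + 0.4² = 0.52.

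**The case against.** The strongest reply is that the numbered three-step procedure is the operative one. It agrees with the splitting section on the validation set, and the sentence in Training of Algorithms is an introductory remark that names the wrong set. This largely stands. A reader might infer that the final performance estimate will be biased. The documents do not support that, because under the three steps the validation estimate is independent of selection. The wrong name still has to be corrected, since it comes directly before the selection rule.

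On tuning, a reader might infer that Step 1 is certainly scored on the fitted rows. That is the natural reading but not the only one: resampling inside the 60% would fit the wording, and an article may leave such detail to a fuller plan. Even with in-sample scoring, Steps 2 and 3 use held-out data, so a poorly tuned model would still have its performance reported honestly. What remains is that the article states two different places for tuning.

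A reader might also take the plural in "the models with the best fit and accuracy will be applied to the validation dataset" to mean that several candidates compete on the validation set. The article covers two programmes and several outcomes, so more than one final model is to be expected, and the plural is not a fault.

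On size, the article relies on a very large dataset, and there the selection optimism is negligible. Survey-linked users in four districts of Madhya Pradesh are the obvious smaller subset. For Kilkari, however, Table 2 ties only logistic regression to those survey data, so a best-of-six choice there is not what the table describes. Objective 2a leaves such a choice possible for the health workers, with no number given.

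**Conclusion.** The point holds as an inconsistency that should be fixed. The validation set has two incompatible roles, and tuning is placed on different sets in different sections. If Training of Algorithms is followed, the final estimate is not independent of selection. Under equal true accuracy of 70% and independent errors, the optimism is about 4 points with 200 validation records and about 0.2 points with 100,000. All these inputs, including the subset sizes, are assumptions, and correlated errors would reduce the figures. If Step 1 is scored on the fitted rows, over-flexible versions are favoured. The illustrative penalty was 7 to 8 points of error, with no decline from 1,000 to 10,000 records. That penalty concerns the quality of the chosen model, not the honesty of its reported performance.

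**What to change.** In Training of Algorithms, replace the validation set with the test set. Then state one sequence in all three sections:

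1. Tune each algorithm inside the 60% training set using held-out scoring (cross-validation or an inner hold-out), not metrics on the rows used for fitting.
2. Choose between algorithms on the 20% test set, and reword the fine-tuning remark in the splitting section to match.
3. Apply one locked model per outcome, once, to the 20% validation set, and report that result as the performance.

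Cross-validation is not essential: tuning on the test set, as the splitting section already has it, would also leave the validation estimate independent. What matters is that one place is stated and that the validation set is used once. The 60/20/20 split stays and no new data are needed. The cost is a few wording changes, some computing time and possibly slightly lower reported performance.

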**Supervised**				
	1 Logistic regression	Classification (nonlinear model)	Classification of ASHA workers by user characteristics and patterns of training initiation by ASHAs	User characteristics associated with exposure to messaging content and duration in MP where face-to-face survey data have been collected
	2 Linear discriminant analysis	Classification (linear model). It is a linearization of Gaussian naïve Bayes.	Classification of ASHA workers by user characteristics and patterns of training initiation, completion, and performance	User characteristics associated with exposure to messaging content and duration
	3 Support vector machines (SVMs)	SVMs are techniques based on the calculation of the maximum margin hyperplane for the classification problems	Classification of ASHA workers by user characteristics and patterns of training initiation and completion	User characteristics associated with exposure to messaging content and duration
	4 Classification and regression trees	Predictive model that consists of leaves that represent the target and branches that represent conjunctions of inputs features. Considered a subset of decision trees. Random forests operate by constructing multiple decision trees during training and aggregating their results to avoid overfitting by single trees.	Classification of ASHA workers by user characteristics and patterns of training initiation and completion	User characteristics associated with exposure to messaging content and duration
	5 Naïve Bayes	Classification model based on probabilities	Classification of ASHA workers by user characteristics and patterns of training initiation and completion	User characteristics associated with exposure to messaging content and duration
	6 Neural Networks (NNs)	NNs are powerful models for machine learning. They are a generalization of linear and nonlinear models	Classification of ASHA workers by user characteristics and patterns of training initiation and completion	User characteristics associated with exposure to messaging content and duration
**Unsupervised**				
	7 K-means	K-means clustering is a way to use data to uncover natural groupings within a heterogeneous population	Grouping of ASHA workers by user characteristics and patterns of training initiation and completion	User characteristics associated with exposure to messaging content and duration

Our choice of methods will include a mix of algorithms based on their strengths and weaknesses and the objective of the process. A comprehensive comparison of supervised learning methods is provided in literature [17,18]. SVM and NNs are expected to perform better with continuous data while the Naïve Bayes method and decision trees perform better with discrete/categorical variables. Naïve Bayes and decision trees have good tolerance to missing values, while NNs and SVM do not. NNs and Naïve Bayes have difficulty handling irrelevant and redundant attributes (ie, extra variables with no useful information or variables with too many categories and too few numbers), while SVM and decision trees are insensitive towards them. Variables with high correlation negatively affect the performance of both Naïve Bayes and NNs, whereas SVM are relatively robust to correlated variables. While Naïve Bayes is robust to noise, NNs are sensitive to poor measurement of variables and susceptible to overfitting. NNs and SVM perform well with multidimensional data and when there is a nonlinear relationship between predictor and outcome. Naïve Bayes requires less memory for both training and validation phase, whereas NN requires large memory allocation across all phases. SVM and NNs usually outperform other methods while Naïve Bayes may yield less accurate results. Table 3 compares the strengths and weakness of different supervised machine learning methods.

